### Interventions

Participants will be randomised into one of the two groups:

Diet group: using an eTRE-MD.Medication group: using N/B.

#### Diet group

Participants in the diet group will follow with a calorie restricted Mediterranean diet, with an eating window between 8 am and 6 pm for a period of 6 months. Participants are asked to stop eating at 6 pm. This results in a daily fasting window of approximately 14 hours. During the fasting time, only calorie-free drinks will be allowed. A daily calorie restriction of 500 kcal will be applied, based on the estimated energy requirement calculated using the WHO equation for participants with a BMI ≤30 and the Harris-Benedict equation for those with a BMI >30.^26^ The diet will be based on the Mediterranean food pyramid,^27^ emphasising high-fibre foods such as fresh fruits and vegetables, unprocessed whole grains, beans, seeds, herbs and spices, while limiting processed foods, red meat, sweets and alcohol. At baseline, participants receive a detailed explanation of the dietary protocol, two sample daily meal plans, recipes and a food-exchange list. Dietary adherence is assessed at the 3-month and 6-month follow-up visits using food diaries in which participants record all foods consumed and the corresponding times. The eating window is additionally evaluated at each visit through a questionnaire assessing the average latest eating time and the number of days per week participants adhere to the fasting regimen. Participants receive guidance from a registered dietitian to support correct implementation of the intervention. Consultations take place during the in-person study visits at baseline, 3 months and 6 months. Throughout the intervention period, participants may also contact the study dietitian by telephone for ongoing support. During the entire programme, 60 min of exercise per day is advised. Physical activity will be measured for 1 week with the Activ8 Activity Tracker GEN2 at baseline and at the end of the study.

#### Medication group

The medication used in the study is N/B to ensure that the comparator reflects weight loss alone, without any additional metabolic or liver-specific pharmacological effects. Participants in the medication group will take N/B (Mysimba) two times per day at a total dose of 32 mg/360 mg N/B per day for a duration of 6 months. The dosage will be built up in the first month following the stepped care approach used in the Summary of Product Characteristics (SmPC), up to maximally tolerated doses. Compliance with N/B intake is monitored by pill counting at the 3-month and 6-month visits. Participants are asked to bring all medicine packaging to each visit, and the number of remaining tablets is recorded by the researcher. Adherence is defined a priori as taking at least two tablets per day, with dose adjustments permitted based on individual tolerance. They receive usual care, including the advice of 60 min of exercise per day and standard dietary recommendations according to the guidelines for the Dutch population.^28^ During the visits at baseline, 3 months and 6 months, medication use and usual care will be evaluated by a physician in the hospital. Participants will wear the Activ8 Activity Tracker GEN2 at baseline and at the end of the study.

### Outcomes

The main study parameter is the between-group difference in absolute change in liver fibrosis during 6 months. Liver fibrosis will be measured as LSM (kPa) by transient elastography (FibroScan).

Secondary study parameters are as follows:

Absolute change in liver steatosis (Controlled Attenuation Parameter score, FibroScan).Nutritional assessment: body weight (kg, Seca 888 compact digital flat scale), height (cm), waist circumference (cm), fat mass and lean body mass measured with bioelectrical impedance analysis (kg, Bodystat 500), grip strength (kg, Jamar).Cardiovascular risk factors: total cholesterol, low-density lipoprotein cholesterol, high-density lipoprotein cholesterol, triglycerides, apolipoprotein B (ApoB), apolipoprotein AI (ApoAI), lipoprotein (a), Hemoglobin A1c, fasting blood glucose, fasting insulin and blood pressure, measured with routine lab procedures.Other laboratory measurements, measured with routine lab procedures. Among others, the following routine measurements will be done: creatinine, eGFR, alanine aminotransferase (ALAT), aspartate aminotransferase (ASAT), thrombocytes, haemoglobin (Hb), leucocytes, transferrin, ferritin, total iron binding capacity, apolipoprotein B48 (ApoB48), fibroblast growth factor 19 (FGF19) and 21 (FGF21), C-reactive protein (CRP), fibrosis-4 index score (Fib-4), thyroid-stimulating hormone (TSH), free thyroxine 4.Physical activity (Activ8 Activity Tracker GEN2).Quality of life (36-Item Short Form Health Survey Questionnaire).^29^Patient satisfaction in case of T2D (Diabetes Treatment Satisfaction Questionnaire).^30^Food intake and adherence to the dietary intervention (3-day food diary).Demographic variables, drug use, smoking and drinking habits, medication use and compliance to the time restriction (self-developed questionnaire).

Other study parameters are as follows:

Shift in liver fibrosis severity (categorised in fibrosis score F0-F3).Side effects (self-reported).Number of participants that drop-out (categorised by reason for drop-out).

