### Eligibility criteria

Inclusion criteria are:

Body mass index (BMI) >30 kg/m2 or BMI >27 kg/m2 and at least one cardiometabolic risk factor (T2D, hypertension, dyslipidaemia).Moderate to severe liver fibrosis, measured as LSM by transient elastography (>7.0 kPa and <13.6 kPa).Aged 18–75 years.Written informed consent,

Exclusion criteria are:

An insufficient comprehension of the Dutch language (spoken and written).Pregnancy, breast-feeding or intention to become pregnant.Participants with an established diagnosis of liver pathology like, but not limited to:Hepatitis B.Hepatitis C.Autoimmune hepatitis.Wilson’s disease.Haemochromatosis.Primary biliary cholangitis.Primary sclerosing cholangitis.Alcoholic liver disease.History of liver transplant, or current placement on a liver transplant list.History of cirrhosis and/or hepatic decompensation, including ascites, hepatic encephalopathy or variceal bleeding.Participants with active HIV infection and/or treatment.Participants with diagnosed malignancies with or without active treatment.Participants with history or pre-existing renal disease (estimated Glomerular Filtration Rate (eGFR) <30 mL/min/1.73 m^2^).Participants with corticosteroid induced diabetes (while still using corticosteroids).Participants using GLP-1 agonists for less than 3 months or not yet on a stable dose.Participants using Monoamine Oxidase inhibitors, opioids and/or methadone (due to contraindication).Known or suspected excessive alcohol consumption (>30 grams/day for males or >20 grams/day for females. One drink is equivalent to 10 grams of alcohol).Previous or planned (during the trial period) obesity treatment with bariatric surgery. However, previous interventions that have resulted in stable weight for at least the past 3 months are allowed.Participants with a history or evidence of any other clinically significant condition or planned or expected procedure that in the opinion of the investigator, may compromise the patient’s safety or ability to complete the study.

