To account for heterogeneity in metabolic profiles, cardiometabolic condition (type 2 diabetes, hypertension, dyslipidaemia or obesity) will be included as a covariate in all primary and secondary outcome analyses. Outcomes will be analysed using linear mixed models with treatment arm, time point (T1 and T2), and their interaction as fixed effects, adjusted for baseline values. An interaction term between treatment arm and cardiometabolic condition will be explored to assess potential differential treatment effects across subgroups. Given the limited sample size, stratified analyses will not be performed unless sufficient power is available. Participants with multiple conditions will be included in the overall model and appropriately coded for subgroup membership. Sensitivity analyses may be conducted to evaluate the robustness of findings in overlapping vs non-overlapping subgroups.

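### Fasting insulin is compared in all participants although insulin-treated type 2 diabetes is eligible: pooling adds noise, and adds bias only if injected doses change differently by arm

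*Protocol article*

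**What the plan says.** **Who can enter.** Under Eligibility criteria, a participant needs a BMI above 30, or "BMI >27 kg/m2 and at least one cardiometabolic risk factor (T2D, hypertension, dyslipidaemia"). Two exclusions bear on diabetes or glucose-lowering drugs: "Participants with corticosteroid induced diabetes (while still using corticosteroids") and "Participants using GLP-1 agonists for less than 3 months or not yet on a stable dose". Insulin treatment is neither excluded nor required to be stable.

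**What is measured.** Under Outcomes, the cardiovascular risk factors include "Hemoglobin A1c, fasting blood glucose, fasting insulin and blood pressure". Table 1 places laboratory measurements at baseline, 3 months and 6 months. The same outcome list does restrict an item when a restriction is meant: "Patient satisfaction in case of T2D (Diabetes Treatment Satisfaction Questionnaire").

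**How it is analysed.** Statistical methods puts all analyses under intention-to-treat and per protocol. It gives every secondary outcome the same linear mixed model with arm, time point and their interaction, adjusted for baseline. It adds that "cardiometabolic condition (type 2 diabetes, hypertension, dyslipidaemia or obesity) will be included as a covariate in all primary and secondary outcome analyses". Insulin use is not a covariate, and no rule for insulin users is stated. Medication use is collected by questionnaire at all three visits (Outcomes; Table 1) but is not linked to the fasting-insulin analysis.

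**The concern.** In someone who does not inject insulin, fasting insulin reflects the person's own secretion. In someone who does, the assay may also register the injected product. How much depends on the product, the assay, the dose and the time since injection. Adjusting for diabetes does not deal with this, because people with diabetes on insulin and not on insulin share the same covariate value.

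Two things are at stake. First, a few high and variable values can dominate the residual variance and the fitted baseline slope, so a real difference is harder to see. Second, if injected doses move differently in the two arms, the measured difference partly reflects the change in injection. The article gives reasons why this could happen. The diet arm has a 500 kcal restriction and a daily fast of about 14 hours (Diet group). The Introduction cites better glycaemic control with early time-restricted eating in type 2 diabetes. The comparator was chosen for having no further metabolic effect (Medication group). Treatment is open. A lower value caused by less injected insulin could then be read as a metabolic benefit.

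**Working it through.** **Reading.** The plan gives no figure on this point, so there is none to reproduce. Side by side: insulin-treated diabetes may enter, fasting insulin has no restriction, the analysis population is everyone randomised, and no model term identifies insulin users. Followed as written, the plan pools users and non-users.

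**Size, by simulation.** The share of users, the assay and the doses are not in the documents, so all inputs below except the arm size are assumptions.

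- Arm size: 35 × 0.9 = 31.5, taken as 32 (Sample size and recruitment: 35 per arm, 10% drop-out).
- Own fasting insulin: mean 18, SD 8 mU/L; correlation of baseline with follow-up 0.6.
- Extra assay signal in users: about 40 mU/L on average (gamma, 1.8 × 22 = 39.6), with random variation between visits.
- Model: linear regression of one follow-up value on arm and measured baseline, 3,000 runs per setting. This simplifies the planned two-visit mixed model and leaves out the cardiometabolic covariate.

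Check with no users: residual SD = 8 × √(1 − 0.6²) = 6.4, so SE ≈ 6.4 × √(2/32) = 1.60, against 1.62 simulated.

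*(a) Doses alike in both arms, true difference −3 mU/L*

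| Users | Mean estimate | SE | Variance relative to no users | Power |
|---|---|---|---|---|
| 0% | −3.0 | 1.62 | 1 | 45% |
| 5% | −3.0 | 2.02 | (2.02/1.62)² = 1.6 | 34% |
| 10% | −3.0 | 2.40 | (2.40/1.62)² = 2.2 | 29% |
| 20% | −3.0 | 2.88 | (2.88/1.62)² = 3.2 | 21% |
| 30% | −3.1 | 3.41 | (3.41/1.62)² = 4.4 | 17% |

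The estimate stays on target; only its precision suffers.

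*(b) True difference 0, injected insulin 30% lower in one arm only*

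| Users | False difference (mU/L) | False-positive rate |
|---|---|---|
| 5% | −0.5 | about 5% |
| 10% | −1.1 | 7% |
| 20% | −2.3 | 11% |
| 30% | −3.5 | 18% |

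Rough hand check: share × 0.30 × 40 mU/L gives 0.10 × 12 = 1.2 and 0.20 × 12 = 2.4, close to the simulated values.

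**The case against.** The strongest reply is that this is detail for the statistical analysis plan: one analyte among dozens, in an article that condenses a fuller document. That would hold if the article were silent. It is not: it fixes the population principle, the model and the covariates for all secondary outcomes, and applying them literally produces the pooled comparison.

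Other points stand in whole or in part:

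- **Fasting insulin is listed as a cardiovascular risk factor.** No insulin-resistance index is named. A misreading as insulin sensitivity is therefore a risk of interpretation, not something the plan states.
- **The number of users and the assay's response are unknown.** If few users enrol, or the assay does not detect their product, the effect is small or absent.
- **The comparator also aims at weight loss.** Doses could fall in both arms, which would shrink any bias.
- **The effect on error rates is modest.** At 5% to 20% users the simulated false-positive rate is about 5% to 11%.

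A reader might infer more than the documents support:

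- *That people with diabetes are a main source of participants.* Diabetes is one of several qualifying conditions and no proportion is given.
- *That the variance rises more than fivefold.* A raw mixture can give this: with 15% users at mean 300, SD 200 pmol/L and others at mean 100, SD 50, the variance is 0.85 × 50² + 0.15 × 200² + 0.85 × 0.15 × 200² = 13,225, against 2,500, a ratio of 5.3. That ignores the planned baseline adjustment.
- *That the comparison is biased as it stands.* With doses moving alike in both arms, randomisation and baseline adjustment leave it unbiased.

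**Conclusion.** The point holds as a minor one. The plan admits insulin-treated participants and compares fasting insulin in everyone, with no means of telling injected from own insulin. The sure direction of the effect, where users enrol and the assay detects their insulin, is lost precision: about 2 to 3 times the variance of the adjusted estimate at 10% to 20% users. Bias is conditional on doses changing differently by arm: about 1 to 2 mU/L at the same shares if they fall 30% in one arm only. These sizes rest on the assumed share of users, assay signal, own-insulin distribution and correlation, and on a simplified model. Liver stiffness, the sample size and the main conclusion are not touched.

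**What to change.** Add one sentence to Statistical methods. Define the fasting-insulin comparison, and any index derived from it, for randomised participants not using insulin at baseline, and show baseline insulin users' values descriptively by arm and visit. Keep participants who start insulin after randomisation in the main comparison, and examine in a sensitivity analysis the effect of setting aside their values after the start.

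The restriction should rest on baseline use only. Excluding people because they used insulin during follow-up would select on a post-randomisation event that treatment may affect, and would weaken the randomised comparison. Baseline use is fixed beforehand, and the Randomisation section says participants learn their allocation after the baseline measurements.

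The cost is a slightly smaller denominator for one secondary outcome, whose result then applies to people not on insulin at entry. The medication data are already collected. No visit, test, eligibility rule or treatment changes, and all other outcomes keep the full population. Stating the rule now also avoids deciding about outlying insulin values once the data are seen.

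### The fibrosis-shift outcome stops at F3 although follow-up stiffness is not capped, so progression beyond F3 would be unclassified or shown as no shift

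*Protocol article*

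**What the plan says.** The Outcomes section of the protocol article has three tiers. The primary outcome is continuous: "The main study parameter is the between-group difference in absolute change in liver fibrosis during 6 months", with the scale given as "Liver fibrosis will be measured as LSM (kPa) by transient elastography (FibroScan". Secondary parameters follow. The third tier opens with "Other study parameters are as follows", and its first item is "Shift in liver fibrosis severity (categorised in fibrosis score F0-F3". No F4 is named, and the article gives no table that links kPa to F-stage.

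Under Eligibility criteria, the inclusion range is "Moderate to severe liver fibrosis, measured as LSM by transient elastography (>7.0 kPa and <13.6 kPa" and the exclusions include "History of cirrhosis and/or hepatic decompensation, including ascites, hepatic encephalopathy or variceal bleeding". Both govern entry. Under Trial design and in Table 1, elastography is repeated at 3 and 6 months. Nothing in the article limits the values that may be recorded then.

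**The concern.** A shift outcome should be able to record movement in both directions from where participants start. Here the listed stages extend below the entry population, which the eligibility criteria describe as having moderate to severe fibrosis, but not above it. The listed range appears to carry an entry restriction over to follow-up, where that restriction no longer applies.

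The Introduction accepts that fibrosis can lead to cirrhosis, and the Objectives say that a more advanced population was chosen on purpose. Movement beyond F3 is therefore a possibility that the protocol recognises. The shift is also the only categorical fibrosis outcome in the article, so it is the natural place to count individual participants who worsen. If the scale is applied as written, that count is incomplete in one direction only.

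**Working it through.** The article states no figure for the shift outcome, so there is none to reproduce. The check is a comparison of definitions, followed by an illustration of how often the gap could matter.

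**Definitions side by side**

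- Entry: stiffness above 7.0 and below 13.6 kPa, with no history of cirrhosis.
- Follow-up: stiffness at 3 and 6 months, with no bound stated.
- Shift scale: F0, F1, F2, F3, with no cut-offs stated.

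Two readings of F3 are possible:

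1. F3 has an upper bound. A follow-up value above it fits none of the four categories.
2. F3 is open-ended. A participant who enters at F3 and worsens is tabulated as F3 to F3, that is, no shift.

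Neither reading lets the table show progression beyond F3. This conclusion does not depend on where the F3/F4 boundary lies.

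F0-F3 is hard to read as a description of baseline stages only. On the protocol's own label every entrant has moderate to severe fibrosis, so F0 is there to record improvement.

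**How often could it matter?**

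Inputs from Sample size and recruitment: mean fall 1.3 kPa (diet) and 0.5 kPa (N/B), SD 1.0 kPa, 35 per arm. Assumptions:

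- The SD is that of individual change.
- Change is normal and independent of baseline.
- 13.6 kPa stands in for the top of F3.
- Baseline is either uniform on 7.0-13.6 kPa, or 7.0 plus an exponential excess of mean 2.0 kPa, cut at 13.6.
- Larger SDs of 2 and 3 kPa are tried as alternatives.

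For the uniform baseline (width 13.6 − 7.0 = 6.6) there is a hand check. With mean change m and SD s,

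P(6-month value ≥ 13.6) ≈ [s·φ(m/s) + m·Φ(m/s)] / 6.6.

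- N/B, m = −0.5, s = 1.0: (0.3521 − 0.5 × 0.3085) / 6.6 = 0.1978 / 6.6 = 0.030. Expected count 35 × 0.030 = 1.05.
- Diet, m = −1.3, s = 1.0: (0.1714 − 1.3 × 0.0968) / 6.6 = 0.0456 / 6.6 = 0.007. Expected count 35 × 0.007 ≈ 0.24.

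Simulation with 1,000,000 participants per scenario agrees with these and adds the skewed baseline. Each range runs from the skewed to the uniform baseline:

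| SD of change (kPa) | Diet: P | Diet: expected of 35 | N/B: P | N/B: expected of 35 |
|---|---|---|---|---|
| 1.0 (protocol) | 0.11%-0.68% | 0.04-0.24 | 0.51%-3.00% | 0.18-1.05 |
| 2.0 (assumed) | 1.11%-4.70% | 0.39-1.64 | 2.24%-8.65% | 0.78-3.03 |
| 3.0 (assumed) | 3.68%-9.87% | 1.29-3.46 | 5.82%-14.44% | 2.04-5.05 |

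At SD 1.0 the chance of at least one such participant in an arm, 1 − (1 − P)^35, is 3.7% to 21.1% (diet) and 16.3% to 65.5% (N/B).

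**Effect on the primary analysis**

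None. A value above 13.6 kPa enters the mixed model as measured. The model reports mean change, however: one participant in 35 who rises by 2 kPa moves an arm mean by 2/35 ≈ 0.06 kPa. The mean therefore includes such a participant but does not make the event visible.

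**The case against.** The strongest reply is that little is lost. The outcome sits in the lowest tier, beside self-reported side effects and drop-out counts, and the Statistical methods section specifies models only for primary and secondary outcomes. No hypothesis, sample size or conclusion rests on it. All of this stands and limits the point to a minor one.

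A second reply is that the article is condensed, and that cut-offs and the handling of extreme values may be set out in the full protocol or analysis plan. That stands for the cut-offs, whose absence here is no fault. It does not answer the stated range, which the article prints as F0-F3.

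A third reply is that the counts rest on assumed baselines, and that change is added independently of baseline. Regression to the mean among those who start near the ceiling would lower them. This also stands, and the table should be read only as an order of size.

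A reader might draw stronger conclusions that the documents do not support:

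- That such a participant certainly has no category. This is only one of the two readings, because the article never says that F3 ends at 13.6 kPa.
- That the worst outcome is concealed. The kPa value remains in the primary outcome, and adverse events are recorded separately.
- That crossing 13.6 kPa is the worst possible shift, or equals cirrhosis. Moving from 13.3 to 13.8 kPa crosses the ceiling on a change of 0.5 kPa, and the article itself says elastography replaces the biopsy gold standard.
- That the table flatters both arms. With about 0 to 1 participant expected per arm at the protocol's SD, no visible distortion between arms has been shown.

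**Conclusion.** The point holds as a minor defect in a stated definition. The scale is closed at F3, while follow-up stiffness is open above it, so progression beyond F3 is either unclassified or merged into F3. Improvement down to F0 is recorded fully. The effect is confined to one lower-tier descriptive outcome, and the continuous primary analysis is untouched.

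The likely size is small: about 0 to 1 participant per arm at the protocol's SD, and up to about 3.5 (diet) or 5 (N/B) only if the SD of change were as large as 3 kPa. These counts depend on the assumed baseline shapes, on reading the planning SD as an SD of change, and on 13.6 kPa as the boundary. The definitional point needs none of these assumptions.

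**What to change.** In the Outcomes section, define the shift outcome as F0-F4, with F4 reachable at follow-up, and confirm that the stage cut-offs are fixed in advance wherever they are recorded. In the results, report by arm the number of participants whose stiffness exceeds the 13.6 kPa entry ceiling at 3 or 6 months.

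The cost is a one-character change to the stage range, one more category in the shift table and one extra count. No new measurement, change of sample size or change to the primary analysis is needed.
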